### Randomization

2.3

Participants will be randomly allocated in a 1:1 ratio to either the intervention group or control group. An independent third-party entity will oversee the randomization process to ensure impartiality.

Additionally, the trial will stratify participants based on the onset period of their stroke: acute to subacute phase (within 1 month of onset) and chronic phase (from 1 month to 6 months of onset) (24). After confirming participants’ eligibility, we will assign each participant a sequential number for group allocation. For each stratum, we will actively allocate participants in a 1:1 ratio to either the intervention or the control group. A secure computerized system will generate an unpredictable and concealed allocation sequence. A blinded researcher will manage this sequence in opaque envelopes, which will be opened after the participant’s enrollment and baseline measurements are complete.

To ensure group balance and methodological rigor within each stratum, we will use permuted blocks of sizes two and four (25). The block size and allocation sequence details will remain confidential and inaccessible to the team members involved in recruitment, treatment, and assessment until the conclusion of the study.

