### Trial design

2.1

This study is a multicenter, prospective, randomized, evaluator-blinded, non-inferiority trial designed to evaluate the efficacy and feasibility of a digital speech therapy application for post-stroke dysarthria (Figure 1). Participants will be recruited from three stroke centers in South Korea: Ewha Womans University Seoul Hospital, Mokdong Hospital, and National Rehabilitation Center. The trial will be conducted in accordance with the Declaration of Helsinki (19) and received ethics approval from the Institutional Review Board (Approval number: EUMC 2023–02-002, and NRC-2023-01-007). It is registered on clinicaltrials.gov as NCT05865106.

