### Blinding

2.4

Due to the nature of speech therapy, the complete blinding of participants to their assigned interventions is challenging. We will implement evaluator blinding to mitigate this issue and ensure unbiased outcome assessments (26). Evaluators will be thoroughly trained to understand the study protocol and recognize potential biases. Their role is to analyze the trial results objectively without influence from other factors. Evaluators will not interact face-to-face with participants. Instead, they will remotely listen to patient recordings via a web system and evaluate the outcomes. This method ensures evaluators focus exclusively on outcome assessment. They will remain unaware of the participants’ group assignments and will not be involved in other stages of the research.

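### Blocks of two and four, with only evaluators blinded and sizes printed despite promised confidentiality, leave 71–75% of allocations guessable to anyone who sees a whole stratum's sequence

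*Protocol article*

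**What the plan says.** All of the following comes from the protocol article.

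- **Ratio and strata** (Randomization): "Participants will be randomly allocated in a 1:1 ratio to either the intervention group or control group", and "the trial will stratify participants based on the onset period of their stroke" into two phases. Centre is not named as a stratification factor, although the Trial design section says "Participants will be recruited from three stroke centers in South Korea".
- **Blocks** (Randomization): "we will use permuted blocks of sizes two and four". How often each size is used is not given.
- **Confidentiality** (Randomization, the sentence after the block sizes): "The block size and allocation sequence details will remain confidential and inaccessible to the team members involved in recruitment, treatment, and assessment", until the study concludes.
- **Concealment** (Randomization): an independent third party oversees the process, and a computer generates a sequence described as unpredictable. "A blinded researcher will manage this sequence in opaque envelopes", and these are opened once enrolment and baseline measurements are done.
- **Blinding** (Blinding): "complete blinding of participants to their assigned interventions is challenging", so blinding is confined to the evaluators.
- **Who knows the arm** (Intervention group; Control group): researchers introduce the application or the workbook, monitor application use daily and follow workbook users daily. They therefore know each participant's allocation once it is made.

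**The concern.** The plan relies on a sequence that recruiting staff cannot anticipate. Two features weaken that.

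First, a block of two or four forces the arms back to balance every two to four participants. The running count within a stratum therefore carries much information about the next allocation. Opaque envelopes stop anyone from reading the next card. They do not stop anyone from inferring it from cards already opened.

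Second, the article prints the block sizes immediately before saying that they are withheld from the people who recruit, treat and assess.

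At stake is selection at entry. Envelopes are opened only after enrolment, so decisions on whom to enrol and when are made before the allocation is known. If those decisions were influenced by a guess, the arms could differ in prognosis from the start. Evaluators who score recordings without knowing the arm cannot undo that.

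**Working it through.** The article gives no predictability figure, so there is none to reproduce.

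**Inputs.** From the Randomization section: sizes 2 and 4, ratio 1:1, strata by phase only. From Trial design: three centres. From Analysis: 76 participants in total. Assumptions: 38 per stratum (half of 76; stratum sizes are not stated) and, for the central figure, both sizes equally frequent.

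**1. Guessing with the whole stratum in view.** The rule is to name the arm that is behind and toss a coin when the arms are level. Expected correct guesses in a block of 2m are m + 2^(2m−1)/C(2m,m) − 1/2.

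- Block of 2 (m = 1): 1 + 2/2 − 0.5 = 1.5, and 1.5/2 = 75.0%.
- Block of 4 (m = 2): 2 + 8/6 − 0.5 = 2.833, and 2.833/4 = 70.8%.
- Equal numbers of each: (1.5 + 2.833)/6 = 72.2%.

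Any mix lies between 70.8% and 75.0%. Simulated lists of 38 give 72.0%.

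**2. What knowing the sizes adds.** A guesser who makes optimal use of the sizes, without being told where blocks end, reaches 72.1% against 72.0%. What changes is certainty. A block of 4 starts with two of the same arm with probability 1/3.

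- The third allocation is then certain: (1/3)/6 = 5.6% of allocations in the long run (5.3–5.4% simulated).
- The fourth can then be deduced too: (2/3)/6 = 11.1% in all (10.6% simulated).

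Both deductions require knowing that no block exceeds four.

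**3. Guessing with one centre in view.** One list per stratum is shared by three centres, with recruitment shares from equal to 60/30/10.

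| Rule applied to own centre only | Correct guesses |
|---|---|
| Own running imbalance | 53.7–54.8% |
| Opposite of own last allocation | 57.3–59.1% |

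**4. Alternatives, whole stratum of 38 in view.**

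| Scheme | Correct guesses |
|---|---|
| Blocks 2 and 4 | 72.0% |
| Blocks 4 and 6 | 68.9% |
| Blocks 4, 6 and 8 | 67.6% |
| Big stick, limit 3 | 57.7% |

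Under big stick the guess beats a coin only when the limit has been reached. The share of forced allocations is therefore 2 × (0.577 − 0.5) = 15.4%. They are certain only to someone who knows the limit and sees the full sequence.

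**5. Size of bias, illustrative only.** Suppose staff act on every guess and enrol someone whose expected change is η points above average when they expect one arm and η below when they expect the other. With correct-guess rate p, the expected difference between arms is 4η(p − 0.5).

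- p = 0.722: 4 × 0.222 = 0.89η (0.88η simulated).
- p = 0.54 to 0.59: 0.16η to 0.36η.

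For an assumed η of 2 to 5 points, full view gives about 1.8 to 4.4 points. Own-centre view gives 0.16 × 2 = 0.3 to 0.36 × 5 = 1.8 points. The stated margin is 19 points. Nothing in the article supports a value of η or says that anyone would act this way.

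**The case against.** The strongest reply is that 72% is a ceiling. It needs someone who sees every earlier allocation in the stratum, in order. The strata ignore centre, and on a shared list staff at one of three centres reach only 54–59%, close to what big stick gives on full view. This stands. The article does not say whether envelope sets are shared or kept per centre, or whether the follow-up researchers work centrally.

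Several stronger readings are tempting and are not supported:

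- *Publishing the sizes is what makes 72% possible.* It is not. Naming the arm that is behind needs no knowledge of block size. Disclosure is a separate inconsistency whose effect is to make some allocations certain.
- *Recruiters can see the allocations and will steer enrolment.* Screening is assigned to stroke specialists, the principal investigator and a coordinator; training and follow-up to researchers. Overlap is plausible in a trial of 76, but it is not stated.
- *Eligibility is largely discretionary.* Neurological stability is tied to an unchanged NIHSS total over 72 hours, cognition to a K-MMSE cut-off, and vision and hearing to named tests. Some judgement remains, mainly on communication and motor skills, and timing can vary.
- *Steering milder cases to the application would favour it.* The primary outcome is a change score, and milder cases may have less room to improve, so the direction is unclear.
- *The trial is open-label.* The article calls it evaluator-blinded.

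It can also be said that confidentiality was meant for the order of the blocks. That order can indeed stay hidden, but the sentence names block size itself. Finally, larger blocks gain only a few percentage points, so the case for a change rests mainly on big stick.

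**Conclusion.** The point holds in limited form, and acting on it is worthwhile. The Randomization section contradicts itself on the confidentiality of block size. Blocks this small, with past allocations known to treating researchers, do not give the unpredictability claimed.

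Predictability runs from about 54–59% (own centre only, shared list) to 71–75% (whole stratum seen), against an ideal of 50%. The lower range depends on the assumed recruitment shares and on the list being shared. The upper range holds for any mix of the two sizes; its central figure of 72% assumes that they are equally frequent. Selective enrolment is a risk that the design leaves open. The article offers no evidence that it has happened or will happen.

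**What to change.** **For any remaining enrolment** (the article does not give recruitment status):

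- Have the independent third party issue a new list without blocks of two. Preferred is a big-stick rule with a maximum difference of 3 per stroke-phase stratum (about 58% guessable on full view). The minimum is larger, varied blocks (about 68–69%).
- Keep the rule, its limit or the sizes in a restricted document. This matters for big stick too, because about 15% of its allocations are forced once the limit is known and the sequence is seen in full.
- Correct the confidentiality statement, since the sizes now in use are public.

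**Cost.** A new list and a short amendment. Under big stick the arms may differ by at most 3 per stratum, so 6 of 76 (41 against 35). The variance factor is then 1/41 + 1/35 = 0.0530 against 2/38 = 0.0526, about 0.6% larger, which is a negligible loss of power.

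**If enrolment has ended:** correct the confidentiality statement and report baseline balance by how predictable each allocation was (arms level, or one arm behind, within the stratum at the time).

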### Blinding

2.4

Due to the nature of speech therapy, the complete blinding of participants to their assigned interventions is challenging. We will implement evaluator blinding to mitigate this issue and ensure unbiased outcome assessments (26). Evaluators will be thoroughly trained to understand the study protocol and recognize potential biases. Their role is to analyze the trial results objectively without influence from other factors. Evaluators will not interact face-to-face with participants. Instead, they will remotely listen to patient recordings via a web system and evaluate the outcomes. This method ensures evaluators focus exclusively on outcome assessment. They will remain unaware of the participants’ group assignments and will not be involved in other stages of the research.

### Intervention methods

2.5

#### Intervention group

2.5.1

Participants in the intervention group will use a digital speech therapy application designed explicitly for post-stroke dysarthria. Participants will use the application independently, without requiring continuous assistance from caregivers or medical professionals. In addition, occasional guidance or support from family members will be permitted. As part of our regular monitoring process, researchers will follow up on the extent of family assistance to ensure it remains appropriate and consistent for the therapy protocol. However, the primary aim is for participants to manage the therapy autonomously. This approach promotes independence and self-reliance during treatment. Participants will engage in speech therapy for 60 min each day, 5 days a week, for 4 weeks. The flexibility of the application should enable participants to complete their therapy in either a single session or multiple sessions throughout the day. Before therapy begins, researchers will introduce the application to participants and guide them through its usage. Additionally, we will provide a manual booklet to ensure that participants can use the application confidently and independently.

As the majority of stroke patients are older adults, the application is designed to be user-friendly (27). It features elder-friendly functionalities and provides progress updates through both text and voice descriptions to ensure accessibility. Design elements such as button size and spacing are tailored to accommodate the potential fine motor and vision challenges faced by older users (28).

Given the variability in speech impairment patterns due to different stroke lesions in post-stroke dysarthria (29), this application provides a personalized approach to speech therapy. When participants log into the application, it prompts them to perform four speech assessment tasks to evaluate their current speech conditions. The application uses a smartphone microphone to measure the ambient noise levels before each task to ensure optimal recording conditions. The assessment proceeds only if the noise level is <50 dB. Four assessment tasks were adapted from traditional dysarthria assessments. Each task comes with detailed instructions and sample demonstrations to help participants perform assessments efficiently.

**Sustained Vowel:** Participants are instructed to sustain the vowels/a/, /i/, and/u/, using their regular speaking tones. Participants are to perform the task twice, and the longer attempt between the two is recorded for analysis (30).**Diadochokinetic (DDK) Rate:** Participants are required to rapidly repeat syllables /pǝ/, /tǝ/, and /kǝ/, along with the sequence/pǝtǝkǝ/ each for at least 5 s. Subsequently, their performance is recorded for analysis (31).**Word Reading:** Participants are asked to read a set of 30 words from the Urimal Test of Articulation and Phonology 2 (UTAP2). The UTAP2 is specifically designed to assess articulation accuracy in Koreans (32).**Passage Reading:** Participants are instructed to read the passage in a comfortable voice at a natural pace. This assessment evaluates the patient’s articulation and overall speech intelligibility. The *Gaeul* Passage is the standard for examining motor speech disorders in South Korea (33).

The recorded speech assessment data will be sent to a web system. The SLPs will review the recorded assessments remotely. This process enables them to identify specific patterns of dysarthric speech impairment using a web system, as shown in Figure 2. Based on these evaluations, a personalized treatment plan specifies the types and levels of exercise required. As an illustration, participants with respiratory impairment may be assigned the “sustained phonation” exercise. SLPs can also set target goals, including phonation duration, volume, and repetition. Conversely, participants struggling with articulation may perform reading exercises. Considering the common articulation error patterns observed in participants with dysarthria, we arranged the minimal pair sets. If a patient has difficulty stopping sounds, the SLP can set minimal pairs such as/p/ and /f/, or/b/and/v/. This plan is then uploaded to the patient’s application. Subsequently, the patient performs the prescribed speech exercises. The therapeutic goals are set at the beginning of each week. Based on the patient’s performance, the difficulty level of the exercises is adjusted during weekly reviews. If a patient completes the therapy tasks for 1 week, the subsequent week’s exercises are prescribed at a higher difficulty level. This adjustment ensures the continuous progression and adaptation of the patient’s improved speech skills.

**Figure 2 fig2:**
[figure not shown]
Digital speech therapy application system overview.

Our digital speech therapy application integrates a comprehensive behavioral speech therapy exercise based on the established literature (2, 34). An introductory video at the beginning of the exercise explains the participant’s objectives and processes. The application provides real-time visual and auditory feedback during exercise to enhance participants’ immediate responsiveness. Moreover, the application utilizes a sophisticated signal processing algorithm to analyze voice data captured via the smartphone’s microphone. This algorithm assesses various speech acoustic variables, such as sound volume, pitch, reading speed, and pronunciation accuracy. Each exercise comes with predefined thresholds against which participant performance is measured. This enables the application to offer immediate and personalized feedback based on the individual’s progress and performance against these benchmarks. Additionally, the participants can listen to their recordings and receive additional feedback. This comprehensive feedback mechanism promotes patient engagement and constant improvement in speech therapy (35). Detailed procedures for the speech exercises are provided in Supplementary material.

Maintaining adherence and continuing to participate in the study is a crucial goal. Researchers will systematically offer direct feedback to participants regarding their performance and adherence. This approach encourages continuous patient engagement throughout the therapeutic process. To maintain patient adherence, the researchers will monitor the daily progress of each patient. Researchers will contact participants whenever a decrease in the usage of the application is observed. They will reach out through text messages or phone calls to understand the reasons behind the reduction in their usage. The researchers will then provide encouragement and support to reengage participants in the therapy process. Additionally, the application features daily and monthly calendars for visual progress tracking. It also records the duration of daily activities, fostering motivation and consistency among the participants. Moreover, the participants are encouraged to contact the research team for assistance with application usage challenges, including user errors and interface navigation. Researchers will promptly respond to concerns communicated via phone, email, or text to offer immediate support in resolving issues.

#### Control group

2.5.2

Participants allocated to the control group will undergo conventional therapy for post-stroke dysarthria over 4 weeks. In the absence of a standard protocol for post-stroke dysarthria treatment in South Korea, we have developed a conventional speech therapy workbook. This workbook integrates various clinically validated behavioral therapy techniques (2, 34). Its content is aligned with the intervention group’s digital speech therapy application to ensure consistency in treatment approaches. Participants will engage in the workbook for 60 min daily, 5 days a week, for 4 weeks to match the intervention group’s treatment dose and frequency. The workbook ensures treatment consistency across the multiple centers involved in this clinical trial. Before starting therapy, the researchers will guide the participants using the conventional therapy workbook.

In line with the intervention group, occasional guidance or support from family members will be allowed. This approach ensures that both groups have access to similar levels of support. By doing so, we promote equality in the treatment conditions across the groups. During regular follow-ups, researchers will monitor the extent and nature of any assistance family members provide. This monitoring will help ensure that the level of support remains balanced and appropriate for both groups.

Researchers will conduct daily follow ups to ensure adherence to conventional therapy workbook. During these interactions, researchers will discuss the participants’ progress, address challenges, and provide support and encouragement to maintain consistent participation in therapy. This approach ensures that the control group receives the same level of attention and support as the intervention group, thereby maintaining trial integrity. After the clinical trial, participants in the control group will also have access to the digital speech therapy application.

### Outcome measurements

2.6

The study will span 4 weeks, and the details are provided in Table 2. Three assessment stages will be conducted during the process.

**Table 2 tab2:** Schedule of enrollment, interventions, and assessments.

	Enrollment	Randomization and allocation	Post-allocation		Close-out
Timepoint	Pre-baseline		Baseline	4 weeks	Post-study
Enrollment					
Eligibility screen	X				
Informed consent	X				
Allocation		X			
Interventions					
Conventional speech therapy					
Digital speech therapy application					
Assessment					
Speech intelligibility			X	X	
Percentage of consonants correct			X	X	
Oral diadochokinetic			X	X	
Maximum phonation time			X	X	
Depression			X	X	
Quality of life			X	X	
System usability					X

Demographic and clinical characteristics will be recorded after enrollment in the study. This initial recording includes demographic data (age and sex), medical history, stroke information (type and location of stroke and post-stroke duration), level of impairment measured using the NIHSS (23), cognitive status determined using the Korean Mini-Mental State Examination (K-MMSE) score (20), and Clinical Dementia Rating (CDR) tests (36). The demographic and clinical characteristics of the participants are shown in Table 3.

**Table 3 tab3:** Variables evaluated at baseline and study period.

Components	Subcategories
Age	Years
Gender	Male / Female
Medical history	Medication history, concomitant disease history (for example, dementia [Alzheimer’s disease, vascular dementia], central nervous system infection [e.g., human immunodeficiency virus, syphilis, Creutzfeldt-Jakob disease], Pick’s disease, Huntington’s disease, Parkinson’s disease, and others).
Medication	Details of concomitantly administered drugs (for example, medications for dementia treatment, central nervous system stimulants, anticholinergics, tricyclic antidepressants, typical antipsychotics, sleeping pills, typical antipsychotics, anxiolytics, antidepressants, and thyroid hormone)
Type of stroke	Ischemic/hemorrhagic
Stroke lesion location	Cortical (for example, frontal, parietal, and so on), subcortical, cerebellum, thalamus, basal ganglia, and so on.
Side of stroke involvement	Left/Right
Time to enroll after stroke	In days
Cognitive function	Korean Mini-Mental State Exam, Clinical Dementia Rating
Neurological status	National Institute of Health Stroke Scale
Visual function	Intact/Non-intact
Hearing function	Intact/Non-intact
Aphasia	Yes/No

Subsequently, the participants will undergo a comprehensive assessment for post-stroke dysarthria. Psychological well-being questionnaires will also be administered to assess depression and quality of life. Participants will engage in the post-evaluation phase 4 weeks after the baseline assessment. We will repeat the speech assessments and psychological questionnaires from the baseline evaluations. Additional evaluations of usability and adherence rates will be conducted.

